# Mobility and strength training with and without protein supplements for pre-frail or frail older adults with low protein intake: the Maximising Mobility and Strength Training (MMoST) feasibility randomised controlled trial protocol

**DOI:** 10.3310/nihropenres.13507.2

**Published:** 2024-04-08

**Keywords:** frail, pre-frail, protein supplements, mobility, strength

## Abstract

Background Frailty is a common syndrome affecting older people and puts them at risk of hospitalisation, needing care or death. First signs of frailty include reduced muscle strength and mobility decline. A key cause of mobility decline as we age is sarcopenia (age related reduction in muscle strength and mass). Poor nutrition contributes to sarcopenia. A shortfall in protein is associated with reduced muscle mass and strength. This may be due to inadequate intake but also because older people have higher protein needs, especially those with multimorbidity. We need to develop effective treatment to reduce or slow the onset of frailty and mobility decline. Exercise is a recommended treatment. Protein supplements to address the shortfall in protein have the potential to enhance the benefit of regular exercise in frail or pre-frail older adults. This has yet to be definitively demonstrated. Aim To establish the feasibility of conducting an RCT evaluating mobility and strength training with or without protein supplements for people over 60 years old who are frail or pre-frail with a low protein intake. Methods A multicentre, parallel, 2-group, feasibility RCT. Participants (recruitment target = 50) with problems walking, low protein intake and classified as frail or pre-frail will be recruited from four NHS Physiotherapy community services. Participants will be randomised (secure computer-generated: 1:1) to receive 24 weeks of mobility and strength training (delivered in 16 group sessions plus home exercises) or 24 weeks of mobility and strength training with daily protein supplements. Primary feasibility objectives are to estimate 1) ability to screen and recruit eligible participants, 2) intervention fidelity, adherence, and tolerance and 3) retention of participants at follow up. Secondary objectives are to 1) test data collection procedures, 2) assess data completeness and 3) confirm sample size calculation for a definitive RCT. Registration ISRCTN Registry (ISRCTN30405954; 18/10/2022).

## Introduction

Frailty is a state of vulnerability to adverse outcomes, including death, hospitalisation and dependence that is not accounted for by known diseases experienced by many people as they get older
^
1
^. According to the Fried Model, muscle strength, muscle mass, and mobility are central to the concept of frailty. The first manifestations include declines in muscle strength and mass, and changes in mobility such as reduced walking speed
^
2
^. These features are commonly recognised by health professional in patients who they consider to be frail
^
3
^ and they are potential treatment targets as we look to develop ways to prevent or slow the onset of frailty in older people to help them maintain their independence and quality of life and reduce health and social care needs. Mobility limitations in older age are primarily due to progressive declines in muscle strength and mass caused by the effects of age on muscle known as sarcopenia. Inactivity also contributes to this decline. The maintenance of good mobility in older age is intrinsically linked to maintaining muscle strength and mass.

Poor nutrition is also thought to contribute to sarcopenia and, therefore, reduced mobility and frailty. A shortfall in protein can lead to loss of muscle mass
^
4
^. The European Society for Clinical Nutrition and Metabolism (ESPEN) recommend that older adults should consume 1-1.2 g protein/kg body weight (BW)/day to support the maintenance of muscle mass and function
^
5
^. Furthermore, ESPEN recommend higher protein intakes of 1.2-1.5 g/kg BW/day in those with chronic disease such as frailty
^
5
^. It is estimated that approximately half of older adults do not achieve 1.0 g protein/kg BW/day
^
6
^.

Exercise including progressive resistance and balance training is a core strategy recommended for addressing reduced muscle strength and mass and mobility decline, which contribute to frailty
^
7,
8
^. However, there is uncertainty as to whether protein supplements are an effective intervention to reverse or slow the onset of frailty or mobility decline. The findings of randomised trials are mixed, and complicated by different settings, samples, formulations, timing, duration and dose
^
9
^. Current evidence suggests that nutritional interventions such as increasing protein intake on their own do not improve frailty status or frailty associated physical performance measures such as mobility in community dwelling older adults
^
10–
12
^. International guidelines recommend that protein supplementation should only be considered when undernutrition is diagnosed (
*e.g.*, insufficient dietary protein) and supplements should be offered in conjunction with exercise
^
9
^. These recommendations are based on low and very low certainty of evidence. Many studies to date have not specifically recruited participants with low protein intake, which may dilute the effect of supplementation on outcomes, nor have they tailored the protein supplementation to individual participants and many only report short term outcomes. There is a need for trials evaluating long term outcomes including cost-effectiveness and outcomes such as quality of life, which are rarely reported
^
8
^.

We have developed and tested a rehabilitation programme that focuses on muscle strength and mobility training
^
13
^, which resulted in clinically significant increases in physical performance
^
14
^. It is possible that these benefits could be enhanced by also optimising poor dietary protein intake. We have designed a randomised controlled trial to test this hypothesis, and which will address the shortcomings of previous trials including targeting a population most likely to benefit from protein supplementation (those with low protein intake), tailoring protein provision, and collecting outcomes needed to make clinical recommendations such as quality of life and health and social care use to estimate cost-effectiveness. However, a fully powered trial would be large and complex and, therefore, a feasibility trial is needed to establish if we can successfully undertake this randomised control trial (RCT).

### Aim

The aim of this study is to establish the feasibility of conducting an RCT to evaluate the clinical and cost-effectiveness of mobility and strength training with and without protein supplements for pre-frail and frail community dwelling older adults with low protein intake.

## Methods

### Trial design

A muti-centred, parallel, 2-group, feasibility randomised (1:1) controlled trial. A study flow chart is presented in
Figure 1. This protocol has been reported following the Standard Protocol Items: Recommendations for Interventional Trials (SPIRIT) statement. MMoST Patient Information Sheet and Consent Form can be found as
*Extended data*
^
15
^.

**Figure 1. f1:**
[figure not shown]
Study flow chart.

### Setting

Participants will be identified from three sources:

1. NHS community trusts.

2. From an existing primary care-based cohort study.

3. Community advertising.

Interventions will be delivered within community physiotherapy services at four NHS sites across England.

### Eligibility criteria

The target population is adults aged 60 years and older who are either frail or pre-frail (as defined by the Fried Frailty Criteria), reporting walking difficulties/slow walking, and low protein intake (<1 g protein/kg BW/day). The full eligibility criteria are described in
Table 1.

**Table 1. T1:** Eligibility criteria.

Inclusion criteria
Aged 60 years and older. Frail (at least 3 criteria) or pre-frail (1-2 criteria) as defined by the Fried Frailty criteria ^ 17 ^. This must include slow walking speed (or difficulty walking). Low protein intake (<1 g protein/kg body weight/day) measured by the average of two 24-hour dietary recall assessments. Willing and able to provide informed consent to participate.
Exclusion criteria
Dementia or cognitive impairment (defined as an Abbreviated Mental Test (AMT) score of 6 or less). Inability to walk 3 m without assistance (walking aid permitted). Unable to follow verbal instructions that would make participation in the exercise group impractical including severe hearing impairment not corrected by a hearing aid or inability to follow simple safety instructions ( *e.g.*, English comprehension). Living in a residential care or nursing home. Pre-existing diagnosis of: ▪ Stroke in the last 6 months. ▪ Parkinson’s Disease. ▪ Acute, unstable physical illness that would make participation in the exercise programme unsafe. ▪ Dysphagia or swallowing problems that requires a modified diet. ▪ Type 1 diabetes or Type 2 diabetes on insulin. ▪ Severe kidney disease (stage 4 or 5). Already taking protein supplements or known allergies to ingredients of protein supplement (milk, soya) or lactose intolerant. Poor kidney function defined by an Estimated Glomerular Filtration Rate (eGFR) of <30 mL/min/1.73m2 (blood test). High risk of developing refeeding problems based upon items from NICE guidance ( https://www.nice.org.uk/guidance/cg32).

### Participant identification

Clinicians such as physiotherapists working in the community trusts will identify potential participants from their current caseload or from waiting lists. They then provide patients with the Participant Information Leaflet (PIL) and seek verbal permission to pass their contact details to the research staff for screening.

We have ethical approval to recruit
*via* an existing cohort study (The Oxford Pain, Activity and Lifestyle (OPAL) study
^
16
^. The OPAL study team will send out invitation letters to potentially eligible OPAL participants (based on response from their most recent questionnaire) living near to study sites and have given permission to be contacted about opportunities to take part in clinical trials. They also send a copy of the PIL and a response form to return to the study team. Interested OPAL participants are contacted by research staff for an eligibility assessment.

We will advertise the study in community venues used by older people that are close to the study sites including retirement living centres and community centres. Posters have a QR code so that interested people can register their interest and give permission to be contacted by the study team or they can telephone the study team.

### Screening

**
*Telephone screening.*
** Initial telephone screening will be undertaken by site research staff. Assessment of frailty is based on self-report by the potential participants using the Fried Frailty Criteria (unintentional weight loss [6 kg or more during the last six months, or 3 kg or more during the last month]; experienced weakness or poor handgrip strength; self-reported exhaustion; slow walking speed (or difficulty walking); and low physical activity)
^
17
^. Frail is defined by the report of at least three criteria and pre-frail by the report of 1-2 criteria. Participants must report slow walking speed (or difficulty walking).

As this initial screening is done over the telephone, verbal consent will be gained to undertake a short dietary questionnaire (
https://proteinscreener.nl)
^
18
^ to assess if protein intake is likely to be low. Verbal consent to undertake this screening will be confirmed and then recorded on the REDCap database before proceeding. Verbal consent was deemed adequate by the Research Ethics Committee. Participants who score at least a 30% risk of low protein intake (<1g/kgBW/day) are eligible to undergo further assessment. We will seek verbal permission to view any blood test results taken within the last three months to check renal function. Potential participants who appear eligible after completing telephone screening will be invited to attend a research clinic assessment at their local site. Potentially eligible participants are asked to complete a 24-hour food diary the day prior to their appointment to aid the dietary assessment to estimate protein intake.

**
*Informed consent, trial specific screening procedures and baseline data collection.*
** Participants will attend a face-to-face research clinic appointment with a researcher. The researcher will provide verbal information about the study and the participants will be given the opportunity to ask questions before being asked to provide written informed consent to undertake the final elements of screening and to take part in the trial. Following consent, cognitive screening using the Abbreviated Mental Health Test (AMT)
^
19
^ and assessment of protein intake will be completed as well as taking a blood test to check renal function if required. We will obtain permission from the participants to inform their GP of their participation. Researchers responsible for consenting participants will be trained in consent procedures and been delegated to do so by the site Principal Investigator.

Estimated daily protein intake will be established by taking the average of two 24-hour dietary assessments using an online dietary assessment tool (myfood24.org)
^
20
^. The first dietary analysis is completed during this appointment. If protein intake is >1.4 g protein/kgBW/day for the first assessment, then they will be excluded at this point as it is unlikely their second dietary assessment will result in an average intake of <1.0 g protein/kgBW/day. The second dietary assessment will be completed after the appointment, which potential participants can complete online or with help from the central study team dietitian over the telephone.

If the participant has not had a blood test in the last three months to check their renal function, then a capillary blood sample will be taken to test Estimated Glomerular Filtration Rate (eGFR) using test kits provided Medichecks.com Ltd. The participant will be asked to complete a baseline questionnaire and undergo physical tests (
Table 2).

**Table 2. T2:** Data collection.

Domain	Measure	Baseline	Weeks 1–16	Weeks 17–24	8 month follow up
Demographic	Date of birth, sex, ethnicity, relationship status, height and weight * (body mass index), index of deprivation (postcode), type of housing, work status, education, carer needs, household income.	x			Height, weight only
Physical capacity	Short Physical Performance Battery (SPPB) ^ 21 ^ (proposed primary outcome)				
Mobility	6-minute Walk Test * ^ 22 ^	x			x
Muscle strength and sarcopenia	Hand grip * ^ 23 ^ and quadriceps strength * ^ 24 ^ measured using dynamometer SARC-F Questionnaire ^ 25 ^	x			x
Frailty	Tilburg Frailty Indicator (TFI) ^ 26 ^ Clinical Frailty Scale Health Questionnaire to calculate the Clinical Frailty Scale Score) ^ 27 ^ Fried Frailty Index based on self-report ^ 28 ^	x			x
Falls	Prevention of Falls Network Europe (ProFANE) self-report of falls and injuries ^ 29 ^	x			x
Comorbidities	Nordic pain questionnaire ^ 25, 26, 30 ^; self-reported health conditions ^ 31 ^	x			x
Protein intake	Assessment of daily dietary protein intake (myfood24.org)	x			x
Renal function	Blood test to evaluate Estimated Glomerular Filtration Rate (eGFR)	x			x
Quality of life	EuroQol Group 5-Dimension Questionnaire (EQ-5D-5L) ^ 32 ^	x			x
Intervention data	Intervention logs; protein supplement review logs (physio and/or dietitian completed) Home diaries: exercise and protein supplements		x	x	
Health Resource Use	Client Service Receipt Inventory ^ 33 ^				x

*Physical tests conducted by researcher

On completion of this appointment, participants will be advised that they may be excluded from the study depending on their blood test results or second dietary assessment.

**
*Confirmation of eligibility assessment.*
** Final eligibility checks will be completed by the central study team prior to randomisation including blood test results, second dietary assessment and whether they risk of refeeding. The central study team dietitian will assess for risk of refeeding using information from the dietary assessment. The central study team will phone the participant if further clarification is needed prior to final confirmation of eligibility.

### Randomisation, blinding and allocation concealment

Eligible participants will be randomised to Mobility and Strength Training or Mobility and Strength Training with protein supplements using a secure (encrypted) centralised web-based randomisation service provided by the Oxford Clinical Trials Unit (OCTRU). Randomisation will be 1:1, stratified by frailty (pre-frail/frail) using variable block sizes within each strata. Following randomisation, the physiotherapy team and the central study team will be notified of allocation
*via* automated email. As we are not using a placebo supplement, it is not possible to blind the participants or physiotherapists delivering the interventions (including provision of supplements). Outcome assessors will be blinded to treatment allocation.

### Interventions

The schedule of intervention delivery is outlined in
Table 3.

**Table 3. T3:** Intervention delivery schedule.

	Mobility and Strength Training	Training + Protein Supplements
Individual pre-class appointment		
Assessment by physiotherapist to establish current ability and exercise setting. Home exercise diary introduced.	X	x
Assessment by physiotherapist to discuss protein supplement dosing and instructions. Provided with written instructions and introduced to protein supplement diary.		x
Delivery of protein supplement arranged.		x
Weeks 1–16		
Weekly group mobility and strength exercises • Group discussion including behavioural strategies to encourage adherence with home exercises (goal setting, exercise planning and problem solving) (15 minutes) • Seated warm up (5 minutes) • Exercise circuit (20 minutes): Strengthening exercises: knee extension, hip extension and abduction, sit to stand Combined hip flexor and calf stretch Balance exercise • Walking circuit (20 minutes) One session of home exercises each week (exercise diary completed). Weights for home exercises are provided if appropriate.	x	x
Protein supplements taken daily. Complete supplement diary.		x
Protein Supplement Reviews including weight checks undertaken at weeks 2, 4, 8, 12 and 16 of the programme. Referral to dietitian if needed.		x
Weeks 17–24		
Twice weekly home exercises. Complete exercise diary.	x	x
3 follow up telephone calls to review progress with home exercises conducted by physiotherapist.	X	x
Protein supplements taken daily. Complete supplement diary.		x
3 telephone supplement reviews during the follow up telephone calls. Weight is not to be monitored.		x

**
*Mobility and Strength Training.*
** All participants will be asked to undertake twice weekly mobility and strength training supported by a physiotherapist for 24 weeks using a combination of weekly group exercise (16 weeks) and home exercises (8 weeks). Group sessions are used to provide supervision and support to participants and promote adherence to long term exercise. This is a pragmatic approach to strength and mobility training that can be implemented within NHS physiotherapy departments without the need for specialist exercise equipment. We have delivered a similar programme for participants with mobility limitations due to spinal stenosis, which was well attended, the exercises were well tolerated and enjoyed by participants
^
13,
34
^.

The programme is progressive and tailored to each participant (
Table 3). Each participant will attend an individual appointment with the physiotherapist prior to attending the group. During this appointment, they undergo an assessment to evaluate their physical ability and are provided with their personal programme to be undertaken during the group sessions. The participants are provided with a workbook containing information about the exercises, exercises diaries and summaries of discussion topics.

Each group session follows the same format beginning with a short group discussion utilising behaviour changes strategies including goal setting and exercise planning to encourage adherence to the programme. Discussion topics include:

The benefits of exercise and physical activityBuilding strengthDealing with aches and pain when exercisingGoal setting and exercise planningStaying steadyMaking exercise and physical activity part of your lifeDigital options to support long term exerciseCelebrate success

Seated warm up exercises are performed. Participants will then undertake an exercise circuit consisting of strengthening exercises focusing on the muscles required for safe walking and uses weights or resistance bands to make the exercises sufficiently challenging. The Borg Rating Scale of Perceived Exertion is used to allow individual tailoring while ensuring the exercise is sufficient to achieve gains in muscle strength
^
35
^. During the strengthening exercises, physiotherapist will ask participants to work at a level of 5-6/10 on the Borg Scale. Over the 16 weeks of group sessions, as muscles strengthen, exercises are progressed by manipulating the load and the number of sets and repetitions to ensure that participants continue to work at the expected level on the Borg scale. Load will be added using ankle weights, hand weights, weight vests or resistance bands. Speed is also added to introduce a power element to the strength training and a means of further progression. Finally, the exercise circuit includes a balance exercise that is progressed in difficulty and a lower limb stretch to ensure adequate mobility at the hip and ankle for walking.

The final element of the exercise programme is a supervised walking circuit. This includes exercises to challenge and improve walking balance and walking practice to increase speed and endurance. Less able participants may start off walking between two points with rest stops.

The exercises performed during the supervised group sessions are also undertaken at home. Participants are asked to complete the programme at home once a week while attending the group sessions. Then, twice per week for a further eight weeks of independent exercise (with three support phone calls). During group discussions and support phone calls, we help participants make a long-term exercise plan. This includes continuing with their home exercises but also considering other activities they may undertake include digital options. Participants will be given access to an existing exercise app (Good Boost:
https://www.goodboost.ai/). Use of the app is completely optional and as part of this feasibility study, we are interested to see how many participants opt to use this type of offering.

**
*Protein supplements.*
** Participants randomised to receive protein supplements will be asked to take the supplements for 24 weeks starting on the day they begin the group exercise sessions. The protein is a powdered supplement (Nutricia Fortifit) produced by Danone Nutricia Research and delivered to participants’ homes. Cold water is added to make up a drink in a shaker (125 ml water per serving). Each serving of the protein powder contains 149 kcal, 20.7 g whey protein, 2.8 g leucine, 20 ug/800 IU vitamin D and 501 mg of calcium. This product has been chosen as it is enriched with leucine, allowing more effective muscle protein synthesis stimulation in a lower serving
^
36
^, and is less calorific than using a pre-prepared protein drink. The main target of the intervention is to increase protein intake rather than energy.

Physiotherapists will provide the supplement to participants with the support of the central study team dietitian. Protein supplements are tailored to each participant based on their baseline protein intake. The aim is for each participant to consume up to 1.6 g protein/kgBW/day. This is slightly higher than the recommended daily protein intake for older adults with acute or chronic diseases to maintain or regain muscle mass (1.2 – 1.5 g protein/kgBW/day)
^
5
^. However, retrospective breakpoint analysis conducted on RCTs exploring the impact of protein supplementation on resistance training-induced gains in fat-free mass (FFM) demonstrated that increases in FFM plateaued at daily protein intakes of 1.6 g/kg/d
^
37
^. If a participant has a BMI of 30 or more, then the recommended dose of protein is 75% of the calculated amount based on weight (as per usual clinical practice)
^
38
^. Additionally, if a participant has an eGFR between 30-60 ml/min/1.73 m
^2 ^(indicating a moderate reduction in renal function), protein intake will be limited to 1.3 g/kgBW/day. This is the maximum dose recommended for this patient group by The Kidney Disease Improving Global Outcomes (KDIGO) guidelines.

On a day when participants undertake Mobility and Strength training (at the hospital or at home), they will be advised to take one of their drinks of the supplement directly after the exercise session. Participants will complete a protein supplement diary to monitor adherence and record any side-effects experienced. Participants will be monitored and weighed at regular reviews (
Table 3). If a participant is experiencing gastro-intestinal problems, then they will be advised to reduce the dose by a half and gradually increase the dose back to the recommended amount over four days to improve tolerance. If a participant has lost >10% of their weight or is reporting ongoing intolerance issues, then participants will be reviewed by the main study team dietitian to decide if the protein supplement dose needs to be adjusted or other dietary advice given.

The chosen supplement also contains vitamin D and calcium. If participants are already taking over the counter supplements, then they will be asked to stop taking them while they are on the protein supplements. If participants are already on prescribed supplements, then the physiotherapist will liaise with the participant’s general practitioner to adjust their prescription to ensure daily maximum doses are not exceeded (Vitamin D: maximum of 4,000 IU per day; Calcium: maximum of 1 g per day).

All participants will attend the same exercise sessions. Supplement reviews will be conducted outside these sessions and participants will be asked not to discuss them in the groups. Groups will be run this way to so sites can fill the exercise groups in a timely way.

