### Primary feasibility outcomes

**
*Progression criteria.*
** Progression criteria into a future definitive trial will be based on the stop-go criteria assessing feasibility detailed in
Table 4 alongside consideration of adverse events and discussions with the Independent Monitoring Committee. The stop-go criteria follow a ‘traffic light’ system: Red (stop), Amber (proceed with modifications) and Green (Go). There are four categories: recruitment, intervention fidelity, intervention adherence and study retention.

**Table 4. T4:** Stop-Go Criteria.

	Red	Amber	Green
Recruitment: Number of participants recruited	< 25 participants recruited within 6 months	25–39 participants recruited within 6 months	>40 participants recruited within 6 months
Intervention fidelity: provision of the mobility and strength training	<50% undergo their individual assessment and are allocated to their group sessions	50% – 80% of participants undergo their individual assessment and are allocated to their group sessions	>80% of participants undergo their individual assessment and are allocated to their group sessions
Intervention fidelity: delivery of the mobility and strength training (fidelity assessment *via* observations based on core criteria checklist)	<50% of all key criteria are met during observed sessions	50–80% of key criteria are met during observed sessions	>80% of key criteria are met during observed sessions
Intervention fidelity: protein supplements	<50% of participants receive the protein supplements *via* home delivery as intended	50–80% of participants receive the protein supplements *via* home delivery as intended	>80% of participants receive the protein supplements *via* home delivery as intended
Intervention adherence: participant attendance at the mobility and strength training	On average, < 8/16 sessions (50%) of sessions attended by 70% or more participants	On average, 8-10/16 session (50–69%) of sessions attended by 70% or more participants	On average, at least 11/16 sessions (70%) attended by 70% or more of participants
Intervention adherence: participant adherence to the protein supplements	On average, 70% or more participants report taking protein supplements on <50% of days over 24 weeks	On average, 70% or more participants report taking protein supplements on 50–70% of days over 24 weeks	On average, 70% or more participants report taking protein supplements on ≥70% of days over 24 weeks

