### Adverse events

Safety reporting will begin from the time of randomisation to 8 month follow up. All study staff have been trained to report adverse events (AEs) related to the study interventions. Given the age of participants, there are foreseeable AEs that should only be reported if they occur during or within two hours of any study interventions. These include acute infections, medical instability (
*e.g.*, worsening of heart failure), vestibular disorders or stroke and fall-related injuries. We anticipate participants may experience delayed onset muscle soreness (<72 hours) upon starting a new exercise programme, which is only reported if they are more persistent or severe than expected. We would also expect that participants taking protein supplements may experience mild gastrointestinal complaints including diarrhoea, constipation, bloating and loss of appetite. Participants are made aware of these, and they should be short lived and managed by adjusting their protein supplement dose. If symptoms are more severe and longer lasting than what is expected, then they will be reportable.

A serious adverse event (SAE) is an untoward medical occurrence that results in death; is life-threatening; requires inpatient hospitalisation or prolongation of existing hospitalisation; results in persistent or significant disability/incapacity; consists of a congenital anomaly or birth defect. We will follow reporting procedures in accordance with Good Clinical Practice (GCP) to report any SAEs that are potentially related to trial procedures.

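### Side-effects are solicited and interim weight is taken in the supplement arm only, so tolerance data will have no like-for-like control figure

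*Protocol article*

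**What the plan says.** All places are in the protocol article.

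- **Side-effect diary.** Interventions, protein supplements: "Participants will complete a protein supplement diary to monitor adherence and record any side-effects experienced". Table 3 marks the supplement diary in the training-plus-supplement column only.
- **Reviews during the classes.** Table 3, same column only: "Protein Supplement Reviews including weight checks undertaken at weeks 2, 4, 8, 12 and 16 of the programme".
- **Reviews after the classes.** Table 3, weeks 17 to 24, same column only: "3 telephone supplement reviews during the follow up telephone calls. Weight is not to be monitored".
- **What both arms have.** A home exercise diary over the whole programme, the weekly classes ("All participants will attend the same exercise sessions"), and "3 follow up telephone calls to review progress with home exercises conducted by physiotherapist". Table 2 schedules weight at baseline and 8 months, without restriction by arm.
- **Adverse events.** "Safety reporting will begin from the time of randomisation to 8 month follow up". The scope is limited by relatedness: "All study staff have been trained to report adverse events (AEs) related to the study interventions". The same section describes mild diarrhoea, constipation, bloating and appetite loss as expected in people taking the supplement. They become reportable only if more severe and longer lasting than expected.
- **Use of the data.** The Abstract names tolerance within the second primary feasibility objective. Progression rests on Table 4 "alongside consideration of adverse events and discussions with the Independent Monitoring Committee".

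**The concern.** Bowel complaints, appetite loss and weight change can occur in frail older people without any supplement. The protocol itself uses unintentional weight loss as one of the Fried criteria at screening. If one arm is asked about such complaints repeatedly for 24 weeks and no equivalent enquiry is scheduled in the other, the recorded frequency in the supplement arm mixes background complaints with any supplement effect, and nothing in the data separates them. Participants and physiotherapists are unblinded, so spontaneous reporting cannot be relied on to even this out.

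At stake is how tolerance is interpreted when the team and the Independent Monitoring Committee discuss progression, and whether a definitive trial takes over the same unequal collection. Testing data collection procedures is a stated secondary objective, so the feasibility trial is the place to find and correct this.

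**Working it through.** **1. Scheduled enquiry by arm (Tables 2 and 3; Interventions).**

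| Source | Training + supplement | Training only |
|---|---|---|
| Diary with a stated side-effect item | 24 × 7 = 168 days | none stated |
| Supplement reviews | 5 (weeks 2, 4, 8, 12, 16) + 3 (telephone) = 8 | none |
| Interim weight | 5 of those 8 reviews | none |
| Home exercise diary | yes | yes |
| Follow-up calls on exercise | 3 | 3 |
| Weight at baseline and 8 months | yes | yes |

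**2. Does general adverse event reporting fill the gap?** It runs over the same period in both arms, but an event must be related to a study intervention. Mild gastrointestinal complaints are discussed only for supplement takers and are not reportable unless worse than expected. A mild complaint in a training-only participant therefore has no planned route into the data. A mild complaint in the supplement arm is caught by the diary and reviews, not by adverse event reporting.

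**3. What background complaints alone could produce.** The target is 50 participants allocated 1:1, so n = 50 / 2 = 25 per arm. The article gives no background rate p; a range of 10% to 40% over the intervention period is assumed, with no supplement effect and full capture in the supplement arm. Expected number recorded = n × p. The chance of at least one is 1 − (1 − p)^25; at p = 10% this is 1 − 0.9^25 = 0.93.

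If the control arm captured only a fraction c of its complaints, the apparent difference would be p × (1 − c). The article does not give c either; one quarter, one half and full capture are shown.

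With equal capture, the 95% half-width for a difference in proportions is 1.96 × √(2p(1 − p)/25). At p = 20% this is 1.96 × √(0.32/25) = 0.222.

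| Assumed p | Expected in 25 | Apparent difference, c = 1/4 | c = 1/2 | c = 1 | 95% half-width, c = 1 |
|---|---|---|---|---|---|
| 10% | 2.5 | 7.5 points | 5 points | 0 | 17 points |
| 20% | 5 | 15 points | 10 points | 0 | 22 points |
| 30% | 7.5 | 22.5 points | 15 points | 0 | 25 points |
| 40% | 10 | 30 points | 20 points | 0 | 27 points |

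The sample size of 50 comes from a cited simulation study and is aimed at the standard deviation of the proposed primary outcome. It was not set for side-effects, and the article gives no inputs from which to reproduce it.

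**The case against.** The strongest case on the other side has five parts.

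- **Tolerance of a supplement is a within-arm question.** The diary and reviews serve adherence and dose adjustment, which do not exist in the training-only arm, and there is no placebo. This stands for the reviews and the weight checks. It does not stand for symptoms: asking about diarrhoea or appetite does not require a supplement.
- **No comparison is planned.** Statistical methods specifies descriptive statistics, with no between-arm side-effect test and no attribution rule. Table 4 has no tolerance criterion. Mild complaints are mostly not adverse events, so no stated rule carries them into the stop-go decision. This stands, and it limits the concern to a risk of misreading.
- **The control arm is not unobserved.** Related adverse events and serious adverse events are reportable in both arms, controls meet the physiotherapists at 16 sessions and 3 calls, and weight is measured at baseline and 8 months. The self-reported Fried index, collected in both arms at those times, gives some further information on weight loss. This stands. A reader might infer that the training-only arm will yield no safety data at all; the documents do not support that.
- **Form contents are not shown.** The exercise diary, intervention log and call script could hold a symptom item. That is possible. But the printed schedule gives the supplement diary and reviews to one arm, and describes the shared calls as being about exercise.
- **Equal collection would still be imprecise.** It would, at about ±17 to 27 points. It removes the difference in enquiry, not the sampling error.

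**Conclusion.** The point holds as an imbalance in ascertainment. Solicited side-effects and interim weight are scheduled in the supplement arm only, and adverse event reporting does not supply the missing control figure for mild complaints. Supplement-arm tolerance data therefore risk being read as supplement-caused.

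The size cannot be fixed from the documents. Under assumed background rates of 10% to 40% and 25 per arm, 2.5 to 10 supplement participants would report complaints with no supplement effect. If controls captured a quarter of theirs, the spurious difference would be 7.5 to 30 points. Both the background rate and the capture fraction are assumptions.

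A reader might go further and infer that the trial is bound to over-attribute complaints to the supplement, or that a significant excess would appear. The plan supports neither: it states no causal conclusion, no between-arm test and no rule linking diary symptoms to progression. This is a cheap improvement to data collection and reporting, not a flaw in the feasibility objectives.

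**What to change.** 1. Add one neutral symptom checklist (diarrhoea, constipation, bloating, appetite loss, other) to the home exercise diary, and ask it in the same words at the three follow-up calls. Both arms already have both. The calls fall only in weeks 17 to 24, so the diary has to carry weeks 1 to 16.
2. Report the checklist descriptively by arm with 95% confidence intervals, stating that about 25 per arm gives wide intervals. Use only this common source for any comparison.
3. Keep the supplement diary and reviews for dose management. Report their symptoms and weights as supplement-arm tolerance only, without causal attribution or comparison with controls.
4. The article describes recruitment as ongoing. If the forms can no longer be changed, apply item 3 and carry items 1 and 2 into the definitive trial.

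Interim weighing of the training-only arm is not required for this fix.

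The cost is one extra block in an existing diary and a short script for existing calls, with no new visits. The downside is slightly more diary and call burden, mainly in the training-only arm. A common checklist does not remove reporting differences due to lack of blinding, since supplement participants are told which complaints to expect; the report should say so.
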